### Study population

We will consider ten sub-populations, based on their prior experience with OAT, in the target trial emulations to identify people who achieve better outcomes from SROM compared to methadone and buprenorphine/naloxone. In each case, the study population will include adults (≥18 years) and exclude those who are pregnant or incarcerated at OAT initiation, and individuals with a history of cancer or palliative care. OAT episodes will be defined as continuous treatment with no gaps exceeding four days for methadone and SROM or five days for buprenorphine/naloxone (see Fig. 1 for details).

These thresholds align with BC guidelines recommending re-titration after these durations.[6] Key sub-populations include (i) incident users – no history of OAT dispensation dating back to January 1, 1996, (ii) prevalent new users – no dispensation for ≥5 days of methadone and SROM and ≥6 days for buprenorphine/naloxone, intended to capture repeated treatment attempts. (iii) prevalent new users – a history of methadone dispensation within past year of the index OAT episode. (iv) prevalent new users – a history of buprenorphine/naloxone dispensation within past year of the index OAT episode, (v) prevalent new users – a history of methadone and buprenorphine/naloxone dispensation within past two years of the index OAT episode, (vi) prevalent new users – completed methadone induction within past two year of the index OAT episode. Induction completion is defined as no dose change within at least two consecutive weeks, (vii) prevalent new users – completed buprenorphine/naloxone induction within past two year of the index OAT episode, (viii) prevalent new users – completed methadone and buprenorphine/naloxone induction during past five years of the index OAT episode, (ix) prevalent new users – individuals initiated treatment with buprenorphine/naloxone, (x) prevalent new users – individuals initiated treatment with methadone (see Table 2 for details).

Pregnant and incarcerated individuals will be excluded since pregnancy requires unique clinical management for treatment interruptions,[6] and incarceration involves distinct treatment protocols.[57]

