## Introduction

### Slow-release oral morphine as an alternative OAT

Methadone and buprenorphine/naloxone are common pharmacological treatments for opioid use disorder (OUD) aimed at reducing unregulated opioid use, overdose risk, and associated harms.[1–10] However, not all individuals respond well to these treatments, necessitating alternative options such as slow-release oral morphine (SROM), extended-release naltrexone, extended-release buprenorphine, and injectable opioid agonist therapies.[6,8,11] Methadone, a full mu-opioid receptor agonist, has long been the gold standard for OAT due to its high retention rates but requires careful dose titration due to its long half-life, overdose risk, and potential for QT (a measure of the heart’s electrical cycle on electrocardiogram) prolongation.[12] Buprenorphine/naloxone, a partial agonist, has a better safety profile but exhibits a ceiling effect on opioid receptor activation, which may limit its efficacy for individuals with high opioid tolerance.[6]

In contrast, SROM is a full agonist with a long-acting formulation which provides stable plasma levels with once-daily dosing without a ceiling on its opioid effects, making it a potential alternative to methadone and buprenorphine/naloxone. Additionally, unlike methadone, SROM does not prolong the QT interval and may have a lower risk of sedation.[13–15] Originally developed for pain management, SROM has gained recognition as an opioid agonist treatment (OAT) in several countries, including Austria, Germany, and Canada, though its regulatory approval status varies. SROM, marketed as Kadian^®^, a 24-hour extended-release morphine capsule, was introduced in 2017 under British Columbia, Canada’s (BC) provincial drug plan (PharmaCare) as an off-label option for individuals who have not found success with methadone or buprenorphine/naloxone, though it is unclear who are most likely to benefit.[5,6]

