### Adapting clinical guidelines to a new drug landscape

Clinical guidelines in BC had previously regarded SROM as a third-line treatment behind buprenorphine/naloxone and methadone but updated their guidance in 2023, in response to rising overdose death rates across the province, to remove the tiers and advise collaborative treatment selection based on client preferences, clinical judgement and contextual circumstances.[6] Guidance for SROM is largely based on clinical consensus and expert opinion due to overall limited evidence to support decision-making.[6] This client-centered shift acknowledges that prior experiences with OAT often shape future treatment decisions. SROM may be an alternative option for individuals who have experienced negative outcomes with other OAT medications, such as incomplete elimination of withdrawal with buprenorphine/naloxone, or intolerable side effects with methadone, including sedation, emotional blunting, or cardiac risks such as QT prolongation.[11] Individuals with contraindications to methadone, including ventricular arrhythmias or concurrent use of QT-prolonging medications, may particularly benefit from SROM as the medication does not affect the QT interval.[11] Moreover, frequent or early switching between OAT options is often a signal of suboptimal treatment fit, whether due to poor tolerability, inadequate therapeutic response, or individual treatment goals not being met.[6,11]

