## Materials and Methods

### Study design

This study is designed as a population-based retrospective cohort study, aiming to emulate a suite of target trials (i.e., hypothetical randomized clinical trials, RCTs) for individuals initiating methadone, buprenorphine/naloxone, or SROM between June 1, 2017, and December 31, 2022, in BC, Canada. This timeline ensures the availability of SROM alongside methadone and buprenorphine/naloxone in BC. Although RCTs are the gold standard for determining comparative effectiveness, they are often time-intensive and may lack generalizability to broader population.[42] By leveraging large-scale health administrative datasets and advanced statistical techniques, observational studies can address many common biases and yield treatment effect estimates based on real-world evidence.[43–46] We will explore the effect variation across key sub-populations which will help identify most beneficiary group from SROM compared to methadone, buprenorphine/naloxone. Key elements of the target trials and their emulations are summarized in Table 1.

This study will utilize population-level data derived from the linkage of nine provincial health administrative databases in BC, where residents are required to participate in a single-payer health insurance system. Using the BC PharmaNet database,[47] which captures daily medication dispensations, we will identify dispensation dates and doses for methadone, buprenorphine/naloxone, and SROM (refer to **S1 Table** for a list of drug/product identification numbers) to define treatment episode. Additional databases include the Discharge Abstract Database[48] (DAD, documenting hospitalizations), Medical Services Plan[49] (MSP, containing physician billing records), BC Vital Statistics [50] (BCVS, capturing deaths and underlying causes), BC Provincial Corrections [51] (recording incarceration entries and releases), Perinatal Care Database[52] (PSBC, covering maternal and infant outcomes), National Ambulatory Care Reporting System[53] (NACRS, documenting Emergency Department visits), Client Roster[54] (providing demographic and geographic data), and the BC Social Development and Poverty Reduction database[55] (tracking social assistance). These datasets are linked at the individual level using a de-identified personal health number assigned by the BC Ministry of Health.[56] A description of these databases and the timeline for data extraction is detailed in **S2 Table**.

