## Figures and Tables

**Fig 1. F1:**
[figure not shown]
Construction of treatment episode for opioid agonist treatment for comparing slow-release oral morphine versus methadone and buprenorphine/naloxone

**Table 1: T1:** Key components of the emulated target trials on comparing the initiation of SROM versus methadone and buprenorphine/naloxone to treat people with opioid use disorder using the observational data

Protocol components	Hypothetical target trial	Emulation of the trial from BC health administrative data
Eligibility criteria	Adults aged 18 years or older who initiated OAT with MET, BNX, or SROM between June 1, 2017, and December 31, 2022. Individuals must not be pregnant or incarcerated and have no history of cancer or palliative care.	The same. To identify people who achieve better outcomes from SROM compared to MET and BNX, we will construct ten study populations to emulate the target trials (see Table 2 for details).
Treatment strategies	*For the study population (i) to (viii)* ITT: Initiating OAT with (1) MET, (2) BNX, and (3) SROM. PP: Receipt of at least 1 dispensation of optimal doses*: week 1: MET (≤40mg), BNX (≤16mg/4mg), SROM (≤240mg); weeks 2 through 3: MET (≥30 mg), BNX (≥12mg/3mg), SROM ((≥140mg); week 4 and beyond: MET (≥80mg), BNX (≥16 mg/4 mg), SROM (≥480 mg)[6] *For the study population (ix)* (1) Switching to SROM within 30 days of BNX initiation, (2) Staying on BNX. *For the study population (x)* (1) Switching to SROM within 30 days of MET initiation, (2) Staying on MET.	*For the study population (i) to (viii)* Treatment initiator effect and PP effect of the same strategies as proposed in the target trials. *For the study population (ix) and (x)* Same strategies as defined in the target trials.
Assignment procedures	Randomization. Prescribers, healthcare teams, and individuals are aware of the treatment status.	Individuals will be classified into treatment strategies based on dispensation records. Prescribers, healthcare teams, and individuals are aware of the treatment status.
Time zero	Date of randomization	Date of first OAT dispensation
Outcomes	Time to OAT discontinuation, along with the time to all-cause mortality and overdose-related acute care visit as the secondary outcomes.	Same.

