Follow-up	Intention-to-treat (ITT): from time zero to outcome, death, loss to follow-up, 24 months after time zero, or December 31, 2022, whichever occurs first. Per-protocol (PP): additionally, we will assess adherence weekly and censor follow-up at protocol violation (see Table 3).	Same.
Causal contrasts	ITT for the sub-populations (i) to (viii) and PP for all.	Treatment initiator analysis for the sub-populations (i) to (viii), and PP for all.
Analysis plan	ITT: Hazard ratios will be estimated using Cox PH model. To obtain risk curves and risk differences at 24 months, we will estimate the baseline hazard and combine it with covariate effects to compute cumulative risks. To adjust for potential selection bias due to loss to follow-up, we will use inverse probability weighting (IPW) as a function of baseline and time-varying covariates. PP analysis: same except that individual are censored at non-adherence and uncensored individuals are assigned IPW that are a function of baseline and time-varying variables.	*For the study population (i) to (viii)* Initiator analysis: Marginal structural models with treatment weights from propensity scores models and censoring weights due to loss to follow-up. Weights will be estimated as a function of baseline and time-varying covariates. PP: Same as initiator analysis except potential pre- and post-baseline confounders that are associated with adherence to the treatment strategies will be included in the censoring models. *For the study population (ix) to (x)* Same PP analysis as applied to the study population (i) to (viii), except that individuals’ clone are used with a modified censoring mechanism (see Table 3).

* The optimal SROM doses are determined applying 1:6 MET-to-SROM conversion rate as per BC guidelines.[6]

**Table 2: T2:** Target study populations for comparative effectiveness analysis

Study population	Definition	Rationale
Incident users	(i) No history of OAT dispensation, dating back to January 1, 1996	To evaluate treatment outcomes among individuals initiating OAT for the first time
Prevalent new users	(ii) No dispensation for ≥5 days of methadone and SROM and ≥6 days for buprenorphine/naloxone	To capture repeated OAT attempts after a washout period, reflecting common real-world patterns.

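### Sub-population (i) has no minimum BC registration before time zero, so recent arrivals treated elsewhere count as first-time OAT users, probably more often in the SROM arm

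*Protocol article*

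**What the plan says.** Under Study population, sub-population (i) is made up of people with "no history of OAT dispensation dating back to January 1, 1996", and Table 2 repeats the rule. Table 2 gives its purpose as studying people who are starting OAT for the first time.

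The remaining eligibility rules are few. The text sets a minimum age and will "exclude those who are pregnant or incarcerated at OAT initiation, and individuals with a history of cancer or palliative care". Table 1 matches: "Individuals must not be pregnant or incarcerated and have no history of cancer or palliative care". Neither place mentions residence or registration in BC before time zero.

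Study design takes OAT history from one provincial source: "Using the BC PharmaNet database,[47] which captures daily medication dispensations". The linked source most likely to show residence is described only as "Client Roster[54] (providing demographic and geographic data", and eligibility makes no use of it. Departure from the province is covered, since the notes to Table 3 list leaving BC among the C2 censoring reasons. There is no matching rule for arrival.

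On the place of SROM in treatment, the Introduction says that it entered the provincial drug plan in 2017 "as an off-label option for individuals who have not found success with methadone or buprenorphine/naloxone". It adds: "Clinical guidelines in BC had previously regarded SROM as a third-line treatment behind buprenorphine/naloxone and methadone", a position that changed in 2023. Accrual runs from June 1, 2017 to December 31, 2022.

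**The concern.** A look-back that starts on a calendar date shows that a person is treatment-naive only if that person could have been seen since that date. Someone treated in another jurisdiction who moved to BC shortly before time zero leaves no trace in PharmaNet and passes the rule for (i). This would be so even with complete BC records back to 1996.

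The same person's covariates are also wrong. Table 4 uses diagnoses recorded at any time, a past-year Charlson index, past-year incarceration and income assistance, and a housing variable whose lowest category pools never with more than five years ago. An empty record falls into the lowest category of each. The treatment weights then treat missing history as good health and stability.

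If the misclassified share were equal in all arms, the cost would be mainly a blurred population. It is unlikely to be equal. Under the guidance in force throughout accrual, SROM was meant chiefly for people who had already tried another OAT, so a SROM starter with no record is more likely to have hidden OAT experience than a methadone or buprenorphine/naloxone starter with no record. The comparison in (i) would then set a partly experienced SROM group against comparators who are more nearly naive.

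**Working it through.** **Check of the rules.** The places where a registration condition could stand were compared.

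- Study population, Table 1 and Table 2: age, pregnancy, incarceration, cancer or palliative care, and dispensing history. No registration or residence condition.
- Table 3: leaving BC is a censoring reason. Entry is not handled.
- Table 4: no covariate for length of registration.
- Table 5: the row on alternative user definitions changes the washout for prevalent new users (14, 30 or 90 days). The incident definition is not varied.
- hdPS estimation: proxies come from BC hospital, billing and dispensing records in the six months before time zero, so they may also be blank for a recent arrival.
- Discussion: the limitations do not mention recent arrivals.

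**Size.** The article gives no count of recent arrivals and no SROM share by true OAT history, so there is no stated figure to reproduce. What follows is an illustration, and every input is an assumption:

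- *m*, the share of apparent first-time users with unseen prior OAT: 1%, 3%, 5% or 10%.
- *s0*, the probability of starting SROM if truly naive: 2% or 5%.
- *s1*, the probability of starting SROM with unseen prior OAT: 10% or 20%.
- *h*, the risk ratio of prior OAT for the outcome: 0.7 or 1.5.

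Formulas:

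- Misclassified share of the SROM arm: *a* = m·s1 / [m·s1 + (1−m)·s0]
- Misclassified share of the comparators: *b* = m(1−s1) / [m(1−s1) + (1−m)(1−s0)]
- Apparent SROM risk ratio when the true one is 1: [1 + a(h−1)] / [1 + b(h−1)]

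Worked case, m = 1%, s0 = 2%, s1 = 10%:

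- a = 0.001 / (0.001 + 0.0198) = 4.8%
- b = 0.009 / (0.009 + 0.9702) = 0.9%
- apparent risk ratio 0.988 (h = 0.7) or 1.019 (h = 1.5)

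Ranges over the four combinations of s0 and s1:

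| m | SROM arm misclassified | Comparators misclassified | Ratio a/b | Apparent RR, h = 0.7 | Apparent RR, h = 1.5 |
|---|---|---|---|---|---|
| 1% | 2.0–9.2% | 0.8–0.9% | 2.1–11.2 | 0.975–0.997 | 1.005–1.042 |
| 3% | 5.8–23.6% | 2.5–2.8% | 2.1–9.6 | 0.936–0.991 | 1.015–1.105 |
| 5% | 9.5–34.5% | 4.1–4.7% | 2.0–8.4 | 0.908–0.985 | 1.023–1.149 |
| 10% | 18.2–52.6% | 8.3–9.5% | 1.9–6.3 | 0.864–0.973 | 1.041–1.213 |

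Two controls on the reasoning. If s1 = s0 (5% each), a = b and the apparent risk ratio is 1.0 at every m, so the bias calculated here depends wholly on s1 exceeding s0. And because s1 is 10–20%, 80–90% of the misclassified people still start methadone or buprenorphine/naloxone. They make up a larger share of the SROM arm because that arm is small in these scenarios.

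**The case against.** *The article is condensed.* A coverage rule could sit in the full protocol, or in S2 Table, and neither is shown. This carries some weight. But eligibility is stated in full in three places and migration is considered at exit, and S2 Table is described as covering the databases and extraction dates, not eligibility. Followed as written, the rule admits these people.

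*SROM had other routes.* The Introduction names methadone contraindications as a reason for SROM and cites a hospital study in which patients with chronic pain were more likely to initiate with it. IV estimation says that initiation with SROM depends largely on prescriber or facility preference. This stands, and it weakens the expectation that s1 is far above s0. A reader might infer that recent arrivals concentrate in the SROM arm. The documents support only likely over-representation: they give no count, and most such people may start a comparator.

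*The planned methods help.* Several Table 4 covariates need no long BC history (age, sex, calendar year, practice size, prescriber funding), time-varying covariates are updated weekly, and the IV analysis targets unmeasured confounding. This stands in part. None of these reveals prior OAT elsewhere, and even a valid instrument would leave the misclassified people in a population labelled as first-time users.

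*The rule should cover every sub-population.* This might also be inferred, but sub-populations (iii) to (viii) require a recorded methadone or buprenorphine/naloxone history, so an arrival with no record cannot enter them. Requiring registration for the whole look-back there would remove people who demonstrably qualify and would correct no misclassification.

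**Conclusion.** The gap is real and specific to sub-population (i): absence of a BC record is taken as absence of prior OAT, and nothing ensures that the person could have been observed. Baseline weighting cannot fully repair this, because the OAT history is unseen and other look-back covariates are coded as absent.

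Over-representation in the SROM arm is a well-grounded expectation from the third-line status of SROM during accrual, but it is not shown. The size is unknown. On the assumptions above, the distortion of a null risk ratio is minor at 1% unseen OAT and reaches 0.864 or 1.213 only at 10% with the widest gap in SROM uptake. The direction is also open, since prior OAT could raise or lower the risk of each outcome. A reader might conclude that the results for (i) will be biased against SROM; the documents do not support that.

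This is a worthwhile improvement to one of ten sub-populations. It does not undermine the study as a whole.

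**What to change.** For sub-population (i) only:

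1. Add to its definition, in Study population and Table 2, continuous BC registration for a stated period before time zero. At least 12 months matches the past-year covariates in Table 4.
2. Add a Table 5 row restricting (i) to people with at least 5 years of registration. This is needed because the 12-month rule still admits someone treated elsewhere 18 months earlier.
3. Report length of registration by arm, so that readers can see whether recent arrivals differ between SROM and the comparators.

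Do not extend a whole-look-back registration rule to (iii) to (viii).

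The cost is small, and the article says that no analyses have been run. Recent arrivals are lost, so (i) would describe established residents. The team must first confirm that the linked registry data hold registration start dates. The article shows that departure from BC can be detected but does not say the same of arrival.

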**Methods::**

We will conduct a population-level retrospective cohort study using linked data from nine provincial health administrative databases. The study population includes adults (≥18 years) in BC who initiated SROM, methadone, or buprenorphine/naloxone between June 1, 2017, and December 31, 2022. Key sub-populations will include incident users with no prior OAT history and prevalent new users with prior OAT experience stratified by OAT type, stability, and medication switching history. The primary outcomes are time to OAT discontinuation and all-cause mortality, while overdose-related acute care visits will be examined as a secondary outcome. To estimate both the initiator effect and the effect of treatment at guideline-recommended doses, we will apply marginal structural models using inverse probability treatment weighting and ‘clone-censor-weights’ approach to address confounding by indication and time-varying confounding. Sensitivity analyses will evaluate the robustness of our findings, including cohort and timeline restrictions, alternative outcome definitions, and alternative estimation strategies including high-dimensional propensity score and instrumental variable approaches.

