Prevalent new users with past OAT experience	(iii) A history of methadone dispensation within past year of the index OAT episode	To assess individuals with recent prior experience of specific OAT which may influence current treatment response.
	(iv) A history of buprenorphine/naloxone dispensation within past year of the index OAT episode	
	(v) A history of methadone and buprenorphine/naloxone dispensation in past two years of the index OAT episode	
Prevalent new users who had previously completed OAT induction*	(vi) Completed methadone induction within past two year of the index OAT episode	To assess individuals recently stabilized on methadone and buprenorphine/naloxone, which may influence response to new treatment.
	(vii) Completed buprenorphine/naloxone induction within past two year of the index OAT episode	
	(viii) Completed methadone and buprenorphine/naloxone induction in past five years of the index OAT episode	A history of completing both inductions may reflect complex needs or higher tolerance, informing comparative effectiveness.
Individuals initiated treatment with buprenorphine/naloxone	(ix) Individuals initiated OAT with buprenorphine/naloxone will be included. Switching to SROM within 30 days of initiation will be compared with staying on buprenorphine/naloxone in a two-arm study.	Early switching within buprenorphine/naloxone episode may indicate suboptimal response or poor tolerability.
Individuals initiated treatment with methadone	(x) Individuals initiated OAT with methadone will be included. Switching to SROM within 30 days of initiation will be compared with staying on methadone in a two-arm study.	Early switching within methadone episode likely reflects adverse effects such as sedation, emotional blunting, or QT-related cardiac risk.

* Induction completion is defined as no dose change within at least two consecutive weeks.

**Table 3. T3:** Censoring indication in the primary and secondary analyses for comparing slow-release oral morphine versus methadone and buprenorphine/naloxone.

	OAT discontinuation		All-cause mortality		Overdose-related acute-care visits	
	Initiator	Per protocol	Initiator	Per protocol	Initiator	Per protocol
OAT discontinuation	outcome	outcome				
End of study ^a^	C_1_	C_1_	C_1_	C_1_	C_1_	C_1_
Death	C_2_	C_2_	outcome	outcome	C_2_	C_2_
Loss to follow-up	C_2_	C_2_	C_2_	C_2_	C_2_	C_2_
Deviation from inclusion/exclusion criteria		C_2_		C_2_		C_2_
Deviation from the protocol		C_3_		C_3_		C_3_

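### Eligibility for sub-populations (ix) and (x) differs between the text and Table 2 on first-time OAT users, and the rule for (ii) needs an explicit prior-OAT condition

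*Protocol article*

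**What the plan says.** **Sub-populations (ix) and (x).** The Study population section defines them as "ix) prevalent new users – individuals initiated treatment with buprenorphine/naloxone" and "x) prevalent new users – individuals initiated treatment with methadone", and refers to Table 2 for details. The abstract contrasts incident users, who have no OAT history, with "prevalent new users with prior OAT experience stratified by OAT type, stability, and medication switching history". Table 2 gives (ix) and (x) rows of their own, outside all the rows headed as prevalent new users. The entries read "Individuals initiated OAT with buprenorphine/naloxone will be included" and "Individuals initiated OAT with methadone will be included". Neither states a prior-OAT condition, and the rationale given for both is early switching within the current episode.

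**Sub-population (ii).** The rule in Table 2 is "ii) No dispensation for ≥5 days of methadone and SROM and ≥6 days for buprenorphine/naloxone". The text describes the cohort as "intended to capture repeated treatment attempts", and the Table 2 rationale is "To capture repeated OAT attempts after a washout period, reflecting common real-world patterns". Table 5 offers three alternative definitions of prevalent new users, each stated only as no OAT dispensation in the past 14, 30 or 90 days.

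**Sub-population (i).** Incident users are those with no OAT dispensation back to January 1, 1996.

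**The concern.** The ten cohorts are organised by prior OAT experience, and the study's question is who benefits from SROM along that axis. For (ix) and (x) the article gives two different answers to whether a first-time user belongs. An early switch to SROM in a first-ever episode and one in a repeat attempt may not carry the same effect, so the two readings target different populations and different estimands.

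There is also an adjustment issue if Table 2 governs. In the clone-censor-weight design both arms are identical at time zero. Imbalance then arises through artificial censoring: the clone assigned to switching is censored at day 30 if no switch has occurred, and the clone assigned to staying is censored at a switch. If prior OAT affects both the chance of switching and the outcome, it has to be in the censoring weights. The Introduction says that BC guidance treated SROM as third-line until 2023, after the whole 2017 to 2022 accrual window, so a link between prior OAT and switching to SROM is plausible.

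For (ii), the question is whether the rule as written keeps it separate from (i).

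**Working it through.** No arithmetic in the plan bears on this point: the article states no cohort sizes, event counts or power. The check compares the definitions.

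**1. (ix) and (x): a first-ever buprenorphine/naloxone starter**

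| Source | Condition | Included in (ix)? |
|---|---|---|
| Study population text, with the abstract's meaning of the label | Prevalent new user, so prior OAT | No |
| Table 2 | Initiated buprenorphine/naloxone | Yes |

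The same comparison for methadone gives the same conflict for (x).

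**2. Covariates if Table 2 governs.** Under factors related to OAT experience, Table 4 lists non-OAT opioid dispensations, prescription opioids before OUD diagnosis, treated tobacco use disorder, attachment to the prescriber, prescriber funding, urine drug testing and practice size. It has no variable for any prior OAT or number of earlier episodes. A footnote to Table 5 mentions treatment interruptions before time zero, but it is keyed to a row on stand-alone practices and adds nothing to the covariate list. As listed, the weights would not account for whether the episode is a first one.

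**3. (ii) and Table 5, applied literally.** Let I be the people with no OAT since 1996, and W(k) the people with no OAT dispensation in the k days before the index episode.

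- Anyone in I has had no dispensation in any earlier window, so I lies inside the (ii) washout set and inside W(14), W(30) and W(90).
- W(90) lies inside W(30), which lies inside W(14). Lengthening the washout removes only experienced users.
- The incident share, size of I divided by size of W(k), can therefore only stay level or rise as k goes from 14 to 30 to 90.

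This describes the rule without its label. Cohorts (iii) to (viii) each write a prior-OAT condition into the rule itself; (ii) does not.

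**4. Size.** If first-time users make up a fraction f of a pooled cohort, the pooled risk difference is roughly (1 − f) × the difference in experienced users + f × the difference in first-time users. The documents give neither f nor either difference, so no figure can be calculated.

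**The case against.** The strongest defence concerns (ii). The label, the purpose stated in the text, the Table 2 rationale and the abstract all say that this cohort is for people with earlier OAT. A first-ever start is neither a repeated attempt nor a return after a washout. The 5- and 6-day rule can be read as marking when a new episode begins for someone already in the prevalent category, and it matches the episode-gap definition in the same section. A reader might infer that first-time users do enter (ii), that (i) is simply contained in (ii), or that the Table 5 analyses mix washout length with OAT naivety. The documents do not support these as statements about the intended analysis. They hold only if the washout rule is coded without its label. It would also be inconsistent to let the abstract's meaning of the label exclude first-time users from (ix) in the text and then ignore that meaning for (ii).

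For (ix) and (x), a reader might infer that first-time users contaminate cohorts meant for experienced people. That takes eligibility from Table 2 and intent from the text. If Table 2 governs, nothing in its rationale says that experienced users are intended. The authors may also have meant that the initial drug is itself the prior experience before the switch. However, at time zero, the first dispensation, a first-ever starter has none, and the label would then mean something different from its use in (iii) to (viii).

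The covariate set is said to be drawn from an earlier methadone versus buprenorphine/naloxone study, which might have handled prior OAT. The text nevertheless gives Table 4 as the list.

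The contradiction over (ix) and (x) stands. It is not detail deferred to a fuller document, because the article itself states both rules.

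**Conclusion.** The text and Table 2 define different eligible populations for (ix) and (x), and these are the only cohorts that address early switching to SROM. The documents do not settle which is intended. If Table 2 governs, whether the episode is a first one is unadjusted in the listed covariates. Calling it a confounder assumes that prior OAT affects both switching and outcome, which is plausible given SROM's third-line status during accrual but is not shown in the protocol.

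For (ii) and the three Table 5 alternatives the point is smaller: the intent is clear and the written rule is incomplete. First-time users could enter only through literal coding.

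The size of any effect is unknown. A dilution figure would rest wholly on an assumed share of first-time users and assumed effects in each group, and would say nothing about this study. The point should be settled before cohort construction, which the Study status section says has not begun.

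**What to change.** 1. **(ix) and (x):** use one wording in the Study population section and Table 2. Either
   - require at least one earlier OAT episode in both places; or
   - keep all initiators of the named drug, drop the prevalent-new-user label, and either stratify by prior OAT or add a prior-OAT variable to Table 4 and to the weight models.
2. **(ii) and the three Table 5 alternatives:** add at least one OAT dispensation before the index episode to the written rule, so that (i) and (ii) are disjoint however the rule is coded.

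The cost is a few lines of wording and a one-line filter using the dispensation history back to 1996 already needed for (i). The downside is somewhat smaller (ix) and (x) cohorts under the first option, or one extra stratified output or covariate under the second. For (ii), nothing is lost relative to its stated purpose.
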